### 2.3. Environmental Data Collection

#### 2.3.1. Meteorological Monitoring

To capture meteorological conditions, we deployed two types of weather stations: a WiFi-based “prosumer” system (Tempest Weather Station, WeatherFlow Inc., Santa Cruz, CA, USA) and a research-grade system (Campbell Scientific Inc., Logan, UT, USA). The Tempest stations record a wide range of variables (Table 2) at 1 min intervals and automatically transmit data to a hub and redundantly log in cloud storage. In summer 2023, six Tempest stations were installed, four at the corners of the site and two near the center, allowing measurements across varied shade and ground-cover conditions.

To ensure accuracy and provide long-term monitoring, a Campbell Scientific research-grade station was installed at the site’s center. This station records many of the same meteorological variables as the Tempest, but its temperature sensor is housed in a fan-aspirated shield to prevent stagnation bias. Data are recorded at 1 min intervals and manually downloaded from the datalogger. A fine temporal resolution is used, corresponding to participant exposure periods as part of the human crossover component. Site-wide microclimatic analysis will use hourly and daily data, which can be aggregated into monthly datasets for long-term analysis. Both the Tempest and Campbell systems collected baseline data until site construction began. The central research station and two Tempest units were removed for construction; the research station was reinstalled in December 2024, while the central Tempest stations were permanently eliminated from the final design (Supplemental Figure S1).

During the second round of clinical trials, before the Campbell station was reestablished, a mobile cart system was developed to replicate the fixed-station measurements. This was done to ensure continuity of meteorological measurements when the central fixed station had to be removed during construction. The mobile unit collected equivalent variables at 1 min intervals and was activated at least 30 min before participant arrival to ensure stabilization. In parallel, one researcher wore an AirBeam3 device during participant walks, providing second-by-second measurements of particulate matter (PM_1_, PM_2.5_, and PM_10_).

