#### 2.9.6. Environmental Data Analysis

Meteorological data from the Tempest and Campbell Scientific stations will be quality-controlled to identify and correct erroneous or missing values. Data will be averaged over 15 min intervals for analysis. Two primary analyses are planned: (1) Intra-park analysis—hourly park-wide temperature averages on synoptically stable days (clear skies and calm conditions) will be compared across stations to identify spatial variability due to shading, ventilation, and ground cover. Anomalies relative to park-wide averages will be correlated with solar radiation, wind speed, and ground cover type; and (2) Post-intervention analysis—post-planting data will be compared with baseline measurements to quantify immediate and long-term microclimate effects of the intervention. Long-term trends will be assessed using the central Campbell Scientific station, with monthly statistics computed for all variables. Data will be compared with other stations in the University of Louisville network and with National Weather Service stations to evaluate the microforest’s contribution to reducing the urban heat island effect. Statistical comparisons will use nonparametric tests (e.g., Wilcoxon rank-sum), with significance defined as *p* < 0.05.

Biological and Ecological Data Analysis Avian data will be analyzed in RStudio (v4.3.1) to compare species abundance and diversity across sites ([name] Microforest, University Quad, Nettleroth Sanctuary). Microsoft Excel will support visualization. Surveys will continue after planting to assess temporal changes in avian presence.

Soil flux data (CO_2_ and CH_4_) will be analyzed using multiple linear regression models, with explanatory variables, including vegetation presence, soil moisture, soil temperature, and photosynthetically active radiation (PAR). Variables showing multicollinearity (r ≥ 0.60) will not be included in the same model. Candidate models will be evaluated using Akaike’s Information Criterion corrected for small sample size (AICc), with models within ΔAICc < 2 considered equivalent.

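### Section 2.9.6 correlates hourly station anomalies with ground cover type, which is fixed at each of at most seven stations, so on the natural reading hours serve as replicates for a station-level factor and the false-positive rate can be badly inflated.

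*Protocol article*

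**What the plan says.** Section 2.9.6 names two primary analyses of the meteorological data. The first is the intra-park analysis, in which "hourly park-wide temperature averages on synoptically stable days (clear skies and calm conditions) will be compared across stations". Its stated aim is to identify spatial variability due to shading, ventilation and ground cover. It continues: "Anomalies relative to park-wide averages will be correlated with solar radiation, wind speed, and ground cover type". The paragraph closes with its one inferential rule: "Statistical comparisons will use nonparametric tests (e.g., Wilcoxon rank-sum), with significance defined as" p < 0.05. It names no station effect, no aggregation to station level and no allowance for clustering.

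Section 2.3.1 gives the size of the network. At baseline, "six Tempest stations were installed, four at the corners of the site and two near the center", and at the centre "a Campbell Scientific research-grade station was installed". After construction the research station was reinstalled, "while the central Tempest stations were permanently eliminated from the final design". The park therefore has at most 6 + 1 = 7 stations at baseline and 4 + 1 = 5 afterwards.

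The same section says the Tempest stations were placed across differing shade and ground cover. It also says that the Campbell temperature sensor is fan-aspirated, and Table 2 lists the Tempest sensors as passively aspirated.

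**The concern.** The three predictors in the correlation step are of two kinds. Solar radiation and wind speed vary over time at every station, so extra hours add information about them. Ground cover is an attribute of the station, and each further hour repeats the same value. For ground cover the replicates are the five to seven stations, however many hours are logged.

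If station-hours are pooled and treated as independent, any lasting offset at a station counts as evidence about its ground cover. The protocol itself describes such offsets. Stations differ in shade, and the one Campbell unit has a different radiation shield. The analysis is restricted to clear, calm days, when shading and aspiration differences are likely to matter most. With so few stations these features cannot be separated from ground cover, so a significant result could not be attributed to it.

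At stake is an unreliable finding about which surfaces cool the park, in an article that presents its results as input to land-use codes and tree ordinances. The problem is clustering by station. It would remain if time-pairing and serial dependence in the before-after comparisons were handled well.

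**Working it through.** The documents state no sample size, power or error rate for this analysis, so there is no figure to reproduce. The check asks how often a pooled-hours test rejects when ground cover has no effect.

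**Inputs from the protocol**
- Stations: 7 at baseline, 5 after construction (section 2.3.1).
- Time unit: hourly, on selected stable days (section 2.9.6).
- Test family and level: rank-sum, 0.05 (section 2.9.6), taken as two-sided.

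**Assumptions not in the protocol**
- Two ground-cover classes, split 3 v 4, 3 v 3 or 2 v 3.
- Hours per station, H: 50 to 480.
- Share of anomaly variance that is a persistent station offset (station ICC): 0 to 0.30.

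**Design effect.** D = 1 + (H − 1) × ICC.
- H = 120, ICC 0.05: 1 + 119 × 0.05 = 6.95.
- H = 120, ICC 0.10: 1 + 119 × 0.10 = 12.9.
- H = 480, ICC 0.10: 1 + 479 × 0.10 = 48.9.

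**Hand approximation.** Subtracting the park-wide mean shrinks the observed variance by (S − 1)/S for S stations but leaves the contrast between classes unchanged. A nominal 5% test therefore rejects with probability about 2Φ(−1.96/√(D × S/(S − 1))). For S = 7:
- ICC 0: D = 1, √(7/6) = 1.080, 2Φ(−1.81) ≈ 7%.
- ICC 0.05, H = 120: √(6.95 × 7/6) = 2.85, 2Φ(−0.69) ≈ 49%.
- ICC 0.10, H = 480: √(48.9 × 7/6) = 7.55, 2Φ(−0.26) ≈ 79%.

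**Simulation.** Station offset plus hourly noise, anomalies taken from the park-wide mean, pooled station-hours compared by rank-sum at 0.05, no ground-cover effect, no autocorrelation:

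| Stations | Hours | ICC 0 | 0.01 | 0.05 | 0.10 | 0.30 |
|---|---|---|---|---|---|---|
| 7 (3 v 4) | 120 | 6.5% | 21% | 47% | 59% | 72% |
| 7 (3 v 4) | 480 | 6% | 47% | 71% | 78% | 89% |
| 5 (2 v 3) | 480 | 8% | 46% | 75% | 78% | 89% |

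Over 50 to 400 hours the rate is about 12-44% at ICC 0.01, 32-70% at 0.05 and 43-79% at 0.10. Five, six and seven stations behave alike. Serial correlation adds to this: with seven stations, lag-1 hourly autocorrelation of 0.7 and no station offset, the rate is already 44-45%.

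**Station as the unit.** For a two-class rank-sum test the smallest attainable exact two-sided p is 2/C(S, k):
- 7 stations, 3 v 4: 2/35 = 0.057.
- 6 stations, 3 v 3: 2/20 = 0.10.
- 5 stations, 2 v 3: 2/10 = 0.20.

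With three classes, an exact Kruskal-Wallis test can reach 0.029 (3/2/2) or 0.043 (3/3/1) with seven stations. It cannot get below 0.067 with six (2/2/2) or 0.20 with five (2/2/1). A t-test on station means keeps its level, at about 5% in simulation.

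**The case against.** The strongest reply is that section 2.9.6 never states the unit of analysis. It names no coefficient and no pooling rule, and nothing in it forbids station means. A condensed article may leave such detail to a fuller document, and the correlation step may be meant as description, since the p < 0.05 rule comes later in the paragraph. It is true that the use of station-hours is inferred. The inference is a natural one all the same. The data are hourly, one step handles two hour-varying predictors and one fixed attribute alike, and the only tests named assume independent observations. For the human outcomes, by contrast, sections 2.9.2 and 2.9.3 do specify random effects and a covariance structure.

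A reader might draw three stronger conclusions, and the documents support none of them.

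- **That the analysis will usually declare a ground-cover effect.** This depends on the ICC and the number of hours, neither of which is given. The rate stays below one half at ICC 0.01, and at ICC 0.05 with about 100 hours or fewer.
- **That a significant result could arise only from counting hours.** The floor above 0.05 belongs to a two-class rank test. The protocol does not fix two classes; sections 2.1 and 2.8.1 mention grass, pavers, shrubs and, later, mulch. Seven stations in three classes, or a t-test on station means, can fall below 0.05 legitimately.
- **That the trial's main results are touched.** The word primary here is internal to the environmental section. Table 1 places heat and pollution under Exploratory Aim 3.

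**Conclusion.** The concern holds in a limited form. Followed on its natural reading, section 2.9.6 treats hours as replicates for a factor that varies only across five to seven stations, and it attributes to ground cover differences that cannot be separated from shade or sensor type. The false-positive rate can then be several times the nominal 5%: about 12-44%, 32-70% and 43-79% at station ICCs of 0.01, 0.05 and 0.10, for 50-400 hours per station. These ranges rest on the assumed ICC, hours and two cover classes. The rate is close to nominal only with neither a station offset nor serial correlation, and the protocol's own account of the stations makes the absence of an offset implausible. The consequence is confined to an environmental analysis under an exploratory aim. Heart rate variability and blood pressure are unaffected, so this should be corrected but does not threaten the trial's main conclusions.

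**What to change.** In section 2.9.6, treat the two kinds of predictor separately.

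- **Ground cover.** Make the station the unit. Reduce each station to one summary anomaly per phase, show the values by cover type with the number of stations in each class, and treat the contrast as descriptive. If it is tested, test it on the station summaries only.
- **Solar radiation and wind speed.** Use within-station regressions, or a model with a station effect that allows for serial correlation within days. If standard errors are clustered by station, add a small-sample correction, because clustered inference on five to seven units is itself unreliable.
- **Wording.** For ground cover, replace 'due to' with 'associated with'.

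No new data are needed. The cost is a revised paragraph, a modest change to the analysis, and the loss of a ground-cover p-value that so few stations can hardly support.

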#### 2.4.3. Soil Sampling and Microbiome Characterization

We are also assessing microbial (bacterial and fungal) community composition and diversity in the microforest over time. This is being done to characterize microbial community health and composition pre- and post-intervention as an exploratory outcome related to ecosystem resilience. Samples were and will be repeatedly taken from the site over time from the same locations; these sample sites cover each corner of the site, as well as the center. From each collected soil sample, we take a 0.25 g subsample of soil and extract genomic DNA using the Qiagen DNeasy^®^ PowerSoil^®^ Kit (Qiagen N.V., Hilden, Germany) following the manufacturer’s guidelines. DNA will be shipped to the W. M. Keck Center for Comparative and Functional Genomics at the University of Illinois, Urbana-Champaign, for Fluidigm amplification, followed by Illumina NovaSeq 6000 sequencing. For bacteria, we will amplify the 16S rRNA region using primer pair V4_515F_806R_New (V4_515F_New 5′-GTGYCAGCMGCCGCGGTAA, V4_806R_New 5′-GGACTACNVGGGTWTCTAAT). For fungi, we will amplify the internal transcribed spacer (ITS) region using primer pairs for ITS1 (ITS1F_ITS2, ITS1F 5′-CTTGGTCATTTAGAGGAAGTAA, ITS2 5′-GCTGCGTTCTTCATCGATGC), and ITS2 (ITS3_ITS4, 5′-GCATCGATGAAGAACGCAGC, ITS4 5′-TCCTCCGCTTATTGATATGC).

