To analyze soil microbiome data, sample inference from amplicon data will first be performed using the DADA2 denoising workflow [64]. DADA2 generates amplicon sequence variant (ASV) tables, which allow for finer resolution than older OTU grouping methods [65]. Bacterial ASVs will then be annotated using the SILVA SILVA_SSU_r138_2019 database [66], and fungal ASVs will be annotated using the UNITE sh_general_release_all_10.05.2021 database [67]. Changes in microbiome community composition over time and in response to other soil properties (e.g., soil nutrients and heavy metal concentrations) will be assessed using principal components analysis. Changes in community diversity over time will be assessed using ANOVA. Indicator species analysis will be performed to identify particular microbial species associated with increased soil health factors and greenness.

Tree inventory data will be analyzed with i-Tree Eco (v6.1.47) to estimate carbon storage and sequestration, pollution removal, oxygen production, and prevented runoff. The results will be aggregated to characterize overall ecosystem services provided by the microforest.

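### Section 2.9.6 names the Wilcoxon rank-sum test for weather data that are serially dependent or paired in time, so its p-values are miscalibrated by an amount and in a direction that depend on aggregation

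*Protocol article*

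**What the plan says.** Section 2.9.6 of the Protocol article sets the working resolution: "Data will be averaged over 15 min intervals for analysis". It then describes several comparisons of station data:

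- within the park, "hourly park-wide temperature averages on synoptically stable days (clear skies and calm conditions) will be compared across stations";
- before against after, "post-planting data will be compared with baseline measurements to quantify immediate and long-term microclimate effects of the intervention";
- long-term trends at the central station, "with monthly statistics computed for all variables";
- outside references, for the heat-island question: "Data will be compared with other stations in the University of Louisville network and with National Weather Service stations".

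One rule closes that paragraph: "Statistical comparisons will use nonparametric tests (e.g., Wilcoxon rank-sum), with significance defined as" p below 0.05. For these tests the section mentions no serial correlation, no matching by time, and no adjustment for season or for year-to-year weather.

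Two other places matter. Section 2.3.1 says the microforest and the parking lot are to be measured concurrently. Section 2.9.5 plans a separate interrupted time series on weekly values, with Fourier terms for season and two references: the site before the intervention and the adjacent parking lot.

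**The concern.** The rank-sum test rests on independence within each sample and between the two samples. Each kind of comparison breaks one of these conditions.

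**Before against after at one site.** Successive 15 min, hourly or daily averages resemble their neighbours, so the effective number of observations is far below the nominal number. The test's standard error is then too small and it rejects too often. A raw contrast of two periods also attributes to the planting any difference in weather between the years.

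**Stations recording at the same times.** Most of the variation is weather that both stations share. Treated as two independent samples, the data appear to carry much more uncertainty about the difference than they do, and the test becomes too conservative.

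At stake is the reading of the microclimate results under Exploratory Aim 3 and the statement on the urban heat island. A significant before/after result could arise with no effect of the planting, and a real difference between concurrent stations could be missed.

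**Working it through.** **Inputs from the article.** Two-sided 0.05 (sidedness is not stated; two-sided is assumed); 15 min, hourly and monthly resolutions (2.9.6). The effect scale of 0.4 °C is the city-wide figure cited in the Introduction and serves only as an illustration.

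**Assumptions.** The article gives no autocorrelations or standard deviations. Series are first-order autoregressive, AR(1), with lag-1 correlation φ over the ranges shown. One summer is 92 days, so 92 × 24 = 2208 hours and 92 × 96 = 8832 quarter-hours.

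**Step 1: nominal level.** With independent data the simulated rank-sum rejection rate is 0.046, 0.052 and 0.053 at n = 12, 92 and 500 per group. The nominal 0.05 is recovered.

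**Step 2: before against after, no true change.** Serial dependence inflates the variance of the comparison by about (1 + φ)/(1 − φ). The approximate false-positive rate is therefore 2 × [1 − Φ(1.96 / √((1 + φ)/(1 − φ)))]. For φ = 0.5 the factor is 1.5/0.5 = 3, and 1.96/√3 = 1.13, which gives 0.258. The simulation at n = 92 also gives 0.258.

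| Resolution | n per period | Assumed φ | Simulated false-positive rate |
|---|---|---|---|
| 15 min | 8832 | 0.98–0.995 | 0.86–0.95 |
| Hourly | 2208 | 0.90–0.98 | 0.67–0.84 |
| Daily | 92 | 0.3–0.8 | 0.16–0.51 |
| Weekly | 52 | 0.1–0.4 | 0.07–0.18 |
| Monthly | 12 | 0.1–0.3 | 0.07–0.13 |

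The effective sample size n(1 − φ)/(1 + φ) shows why finer data do not help:

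- 92 days at φ = 0.6: 92 × 0.4/1.6 = 23
- 2208 hours at φ = 0.95: 2208 × 0.05/1.95 = 57
- 8832 quarter-hours at φ = 0.99: 8832 × 0.01/1.99 = 44

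Adding a random year-to-year shift with SD 0.3 of the series SD raises the daily rate at φ = 0.6 from 0.32 to 0.56, and the monthly rate at φ = 0.2 from 0.09 to 0.20.

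**Step 3: concurrent stations.** Each station is shared AR(1) weather (SD 3, 5 or 9 °C) plus its own noise, with an SD of 0.7 °C for the difference. With no difference between stations, rank-sum rejected in 0% of runs in every setting. Its power for a 0.4 °C difference was:

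| Data | n per station | SD 3 | SD 5 | SD 9 |
|---|---|---|---|---|
| Monthly | 12 | 0 | 0 | 0 |
| Daily, one summer | 92 | 0 | 0 | 0 |
| Hourly, 5 stable days | 120 | 0.03 | 0 | 0 |
| Hourly, 20 stable days | 480 | 0.56 | 0 | 0 |
| Hourly, one summer | 2208 | 1.00 | 0.99 | 0 |
| 15 min, one summer | 8832 | 1.00 | 1.00 | 1.00 |

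The pattern follows from the statistic. Shared weather cancels, so z is close to its expected value, √(6n) × [Φ(δ/(√2 × SD)) − 0.5]. For δ = 0.4 and SD = 3 the bracket is 0.0376, and z reaches 1.96 near n = (1.96/0.0376)²/6, about 453. For SD 5 and 9 the crossing is near 1257 and 4073. Below it the test almost never rejects, and above it almost always.

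**Step 4: is pairing alone enough?** A signed-rank test on differences assumed independent has power 0.37–0.42 at 12 monthly pairs and 1.00 at 92 daily pairs, with a false-positive rate of about 0.02–0.07. With lag-1 correlation 0.5 in the differences, it falsely rejects in 20–32% of runs. Serial dependence has to be handled as well.

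**The case against.** **The test is only an example.** The wording leaves room for other nonparametric tests, and the intra-park analysis also uses departures from the park-wide mean, which remove shared weather. Both points are fair. But those departures are to be correlated with site conditions, the only test named is the unpaired one, and no paired or dependence-aware method appears for these comparisons.

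**Section 2.9.5 already plans the proper analysis.** In part it does: weekly values, seasonal terms and a parking-lot reference deal with much of the before/after question. It does not mention residual autocorrelation, and 2.9.6 lists its own post-planting comparison without deferring to it. Nor does it cover the intra-park comparison across stations or the comparison with the university and National Weather Service stations.

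**The inflation depends on unstated inputs.** This stands. The correlations and SDs are assumed, and at monthly values, the resolution given for long-term trends, the inflation is modest unless year-to-year shifts are added.

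Three stronger readings are tempting, and the documents do not support them:

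- A reader might infer that rank-sum has almost no power between concurrent stations in general. At 15 min resolution over a full summer it detected 0.4 °C in every run, because the large n outweighs the lost pairing.
- A reader might infer that these tests decide Exploratory Aims 3 and 4. For Aim 3, 2.9.5 says the time series estimates the intervention effect. For Aim 4, the greenhouse-gas fluxes use regression with AICc, ecosystem services use i-Tree, and rank-sum is not assigned to any of its outcomes.
- A reader might see the same error in the soil analysis, since "Changes in community diversity over time will be assessed using ANOVA" while "Samples were and will be repeatedly taken from the site over time from the same locations". But ANOVA can include location as a block or repeated measure, and a condensed article may leave that to the full plan.

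**Conclusion.** The concern holds in this form: the test named in 2.9.6 ignores serial dependence and time pairing, and its p-values should not be read at face value. Before against after, the error runs towards false positives: severe at 15 min and hourly resolution, substantial at daily, modest at monthly. Between concurrent stations it is conservative when there is no difference. Whether a true 0.4 °C difference is missed depends on the number of values and the spread of the weather.

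The direction of each error follows from the design. The sizes rest on AR(1) series, the φ ranges shown, weather SDs of 3–9 °C and an SD of 0.7 °C for the station difference. The consequence is limited to exploratory microclimate results; the primary mixed models for heart rate variability and blood pressure do not use these tests. The change is still worth making before the environmental data are analysed.

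**What to change.** In 2.9.6, replace the rank-sum rule with the following:

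1. Form the concurrent difference, park minus reference. The reference may be the parking lot, a university network station or a National Weather Service station; for the pre/post contrast it must have records in both periods.
2. Aggregate the differences to daily or weekly values.
3. Use an autocorrelation-robust method (AR(1) generalised least squares, Newey-West standard errors or a block bootstrap) for both the pre/post and the between-station comparisons. A plain paired test is not sufficient for the latter.
4. In 2.9.5, state that the interrupted time series allows for residual autocorrelation, and say how its result relates to the post-planting comparison in 2.9.6.

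The cost is a little more analysis work on station data already collected or planned. No new measurements are needed.

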### 2.8. Greening Intervention: The [name] Microforest

#### 2.8.1. Site Preparation and Infrastructure

The intervention began after completion of the first round of baseline testing in Summer 2023. Initial site modifications included the removal of the existing central walkway and the installation of a semi-circular retaining wall, along with a new perimeter walking path (Figure 5). The retaining wall is three feet tall and spans 188 feet, and the wall’s thickness varies from one to two feet to support the weight of the new soil. Benches and lighting were added, and the retaining wall was backfilled with approximately 700 tons of Nugent soil to create a three-foot raised area sloping southward. In addition, metal signage and fins were installed on the south side of the retaining wall to complete the circle, with the signage being 66 inches in height and four inches thick, and the metal fins being 60 inches in height and one inch thick (Supplemental Figure S2). This middle well zone was planted with grass, and mulch was applied along the park’s edges prior to the wave 2 physiological assessment in Summer 2024.

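### Soil community composition is assigned to principal components analysis alone, which neither estimates nor tests change over time or response to soil properties (minor, exploratory Aim 4)

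*Protocol article*

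**What the plan says.** Section 2.9.6 puts two questions about the soil community, "Changes in microbiome community composition over time and in response to other soil properties" (nutrients and heavy metals are the examples given), and answers both with one method: they "will be assessed using principal components analysis".

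Two other soil analyses are named beside it:
- For diversity: "Changes in community diversity over time will be assessed using ANOVA"
- For single species: an indicator species analysis, meant to find microbes linked to better soil health and to greenness.

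Section 2.4.3 gives the sampling design. Samples are "repeatedly taken from the site over time from the same locations", and "these sample sites cover each corner of the site, as well as the center". The purpose is to describe the community "pre- and post-intervention as an exploratory outcome related to ecosystem resilience". Table 1 lists microbiome composition as a pre/post outcome of Exploratory Aim 4.

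Section 2.8.1 matters for the likely size of any change: "the retaining wall was backfilled with approximately 700 tons of Nugent soil".

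**The concern.** PCA finds the directions of largest variance in the abundance table. Neither sampling date nor any soil property enters the calculation, so it yields no effect estimate, confidence interval or p-value for them. It can show a pattern, but it cannot settle whether composition changed or whether it follows soil properties.

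The design adds a second difficulty. The same few locations are sampled repeatedly, so lasting differences between them are a source of variance that PCA keeps. If these differences are large relative to the change after planting, they take the first axes and the change does not appear there.

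At stake is one named outcome of Aim 4. The hypothesis that the microforest enhances ecological function could not be tested on composition as the text stands.

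**Working it through.** **Do the other soil analyses fill the gap?** The ANOVA concerns diversity, and composition can turn over while diversity stays the same. The indicator species analysis links single species to soil health and greenness, and does not name time. Neither tests whether composition changed between periods.

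**When would a shift be hidden?** The documents give no figure for the microbiome, so there is nothing to reproduce, and what follows is illustrative. Only the locations come from the documents (corners plus center, read as 5). The rest is assumed: T = 4 or 6 dates, half before and half after planting; 200 taxa on a transformed scale; residual SD 1; between-location SD 0.5, 1 or 2; a common shift with per-taxon SD 0 to 2; 150 runs per setting.

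Model for location l, date t and taxon k: x = a(l,k) + post(t) × d(k) + e.

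A rough threshold follows from the sums of squares per taxon:
- Five locations span 5 − 1 = 4 axes, each carrying about T × (location SD)².
- The pre/post direction carries about (5T/4) × (shift SD)².
- These are equal when shift SD / location SD = √(4/5) = 0.89, whatever T is.

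Below that ratio the shift tends to fall behind the four location axes. Above it, the shift moves to the front.

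The simulated share is the R² of an axis score on pre/post (between-group over total sum of squares). The test compares pre and post mean vectors by squared Euclidean distance, with 199 permutations within location.

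| Shift SD relative to location SD | Pre/post share, better of axes 1-2 | Best of axes 1-6 | Test rejects at 0.05 |
|---|---|---|---|
| No shift | 0-1% | 6-12% | 4-8% |
| Half or less | 0-1% | 54-96% | 92-100% |
| 0.6 (0.3 against 0.5) | 3-5% | 41-48% | 96-99% |
| Equal | 48-66% | 54-69% | 100% |
| Twice | 97-99% | 97-99% | 100% |

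In the second row, location explained 98-100% of the better of axes 1-2.

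**New soil at one point only.** The article does not say which sampling points received new soil. I added a center-only post shift (SD 2 or 4) to a common shift (SD 0.3 or 0.5), with location SD 0.5 or 1. Pre/post then explained 6-37% of the better of axes 1-2, and the test rejected in 65-100% of runs. PCA would show the center's change but would not separate it from a site-wide one.

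**A limit of this check.** The model has no variation shared by all locations on one date, such as weather or season. With such variation (SD 0.2, 0.3 or 0.5, location SD 1) and no shift, the same test rejected in 36-43%, 85% and 100% of runs. The detection rates in the table therefore assume negligible date-to-date variation.

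**The case against.** A reader might infer that location differences will dominate the leading axes and that a real shift would be missed. The documents do not support this. They give no variances, and PCA follows whichever source is largest. About 700 tons of imported soil, mulch at the edges and dense planting could make the pre/post change the largest source, and the table then shows it clearly on the first axes. Nothing limits inspection to two axes, and a shift behind the location axes often shows on a later one. The diversity and indicator species analyses may also reveal related change. Nor does the plan state a test on the first two axes, so no power figure can be attached to the plan as written. All of this stands, and it confines the point to what PCA cannot do and what it may hide.

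It can also be said that a condensed article may leave the companion test to a fuller plan. That lowers the severity but does not remove the point. The article does choose a method for this question, while it names inferential methods for its neighbors: ANOVA for diversity, multiple regression with AICc for gas flux, and Wilcoxon tests for weather data. Regressing axis scores on time would be a test of a kind, but it is not stated, and it would still depend on where the shift falls among the axes.

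**Conclusion.** The point holds in a limited form. As written, change in composition over time and its relation to soil properties would be described but neither estimated nor tested. This follows from the method and needs no assumption about the data.

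Whether a shift would also be hidden on the leading axes depends on its size relative to the location differences, which the documents do not give. Under the assumed inputs it is hidden on the first two axes at half the location SD or less, partly visible when the two are equal, and plain at twice.

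Severity is minor: one outcome of an exploratory aim, with no bearing on heart rate variability or blood pressure.

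**What to change.** Keep PCA for display. Add that pre/post change in composition will be tested by PERMANOVA or partial redundancy analysis on transformed ASV abundances, with period as predictor, location as block and permutations restricted within location.

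Assess soil properties in a separate model, also blocked by location. Do not adjust the period effect for them: the imported soil may have changed nutrients and metals, and adjustment could then remove the shift being sought.

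The permutation scheme should be matched to the sampling dates, which the article does not give:
- One sample before and one after at each of 5 locations gives 2⁵ = 32 arrangements. A full swap leaves the statistic unchanged, so the smallest p-value is 2/32 = 0.0625.
- Two before and two after give 6⁵ = 7,776 arrangements, which is ample if date-to-date variation is negligible.
- If it is not, whole dates should be permuted together, identically at every location. Four dates give 6 arrangements (smallest p = 2/6 = 0.33), six give 20 (2/20 = 0.10) and eight give 70 (2/70 = 0.029). With few dates, an estimate without a formal test is the more honest report.

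The cost is slightly more analysis on the same ASV table, with no new samples for the analysis itself. The choice is best fixed before the post-planting sequences are examined. The test would show that composition differed between periods; with one planted site, it would not by itself show that planting was the cause.
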